#### Supplementary analyses

Before fitting our primary analysis model, we need to identify appropriate auxiliary variables to include in the imputation model. Such auxiliary variables should have information about the missing outcome. Specifically, an independent statistician will use a data set without the treatment variable and perform regression analyses to identify key predictors of outcomes and which combination of baseline variables and time to negative STI test in clinic should be included as auxiliary variables in the imputation model. We will supplement this by performing and reporting a complete case analysis (where any participants with missing information on any covariate or outcome shall be excluded).

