#### Secondary outcomes at 1 year

STIs

Diagnosed with any STI after joining the trial according to self-report confirmed by postal test results and clinic records.

Behaviours

Condom use at last sex.Number of sexual partners since joining the trial.Sex with someone new since joining the trial.Condom use at first sex with most recent new partner.Self-reported sexually transmitted infection testing for self - prior to first sex with most recent new partner.Sexually transmitted infection testing for self - prior to first sex with most recent new partner (confirmed according to clinic record that testing occurred).Participant’s report as to whether their most recent new partner was tested for sexually transmitted infection prior to sex with them.Number of sexual partners since joining the trial.Reading and sharing of intervention content.Number of text messages read.Whether anyone else read the messages, if yes how did the participant feel about them reading the messages?Reading someone else’s messages in the trial (to be reported for control group participants).Someone else in the trial reading participants’ messages (to be reported for intervention group participants).

Potential harms

Car accident where the participant was the driver in the past year.^30^
Experience of partner violence in the past year.^31^

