### Data collection

The primary outcome will be assessed using chlamydia and gonorrhoea tests collected by post at 1 year and clinic records of completed tests. STI test kits for chlamydia and gonorrhoea will be posted (in P650 standard packaging) to respondents. Directions in the pack will ask participants to provide a vaginal swab (women), a urine sample (men) and additional anal and pharyngeal samples (men who have sex with men) and post it in the prepaid and addressed envelope to the laboratory. Test kits will be identified by lab number only, rendering the laboratory staff blind to the participant’s allocation. The accredited laboratory will destroy samples after testing is completed.

Results of the STI testing will be reported on the secure trial lab site by lab code only. Clinical records will be checked to identify participants who have had a positive STI diagnosis since joining the study, confirm self-reported STI testing and partner attendance for treatment.

At 4 weeks and at 1 year, postal questionnaires will be sent to all participants to collect self-reported data. Non-responders will be contacted by any method the participant agrees to at enrolment (post, email, text message, telephone call). Participants can directly enter self-reported outcome data via a web-based data entry form. Paper based self-reported outcome data or self-reported data collected by telephone will be directly entered into the web-based data entry form by a trial assistant blinded to treatment allocation.

Participants will be sent a £5 unconditional incentive with each postal request, that is, when sending the 4 weeks questionnaire and 1 year test and questionnaire. Participants who return the test sample will be sent £20. See figure 2 for the Schedule of enrolment, interventions and assessments. All outcome data will be collected on participants who choose to stop messages unless they withdraw from the trial.

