### Analysis

A detailed statistical analysis plan (SAP) will be finalised and submitted to the TSC before the end of the trial and unblinding. For the primary outcome and other binary outcomes, we will estimate any differences between the groups using logistic regression and we will report ORs with 95% CIs and p values, adjusting for key baseline predictors of outcome. These will be specified in advance in the SAP. For continuous outcomes, we will use linear regression to test for a difference in mean scores between the arms. All analyses will be based on the intention-to-treat principle.

For the primary analysis Multiple Imputation by Chained Equations (MICE) will be used in order to account for missing data.^33^ MICE makes appropriate assumptions for accommodating missing data in the analysis based on the predictors of outcome and the predictors of loss to follow-up. MICE is recognised as a way of reducing bias and increasing precision of trial results and is increasingly used as the primary analysis in randomised controlled trials.^12 33^ One hundred imputed data sets will be generated and the point estimates and SEs will be combined using Rubin’s rules. We will perform information-anchored sensitivity analysis using the delta-method.^34^

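### The candidate auxiliary variables for the primary imputation leave out the questionnaire data, above all the 1-year self-reported STI diagnosis, and the selection step does not look for predictors of missingness

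*Protocol article*

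**What the plan says.** All references are to the protocol article.

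- **Analysis.** "For the primary analysis Multiple Imputation by Chained Equations (MICE) will be used in order to account for missing data". The assumptions of the method are described as "based on the predictors of outcome and the predictors of loss to follow-up". One hundred imputed data sets are combined by Rubin's rules, and a delta-method sensitivity analysis is planned.
- **Supplementary analyses.** The criterion for an auxiliary is given first: "Such auxiliary variables should have information about the missing outcome". The next sentence makes this specific. An independent statistician, working without the treatment variable, runs regressions to find key predictors of outcomes and to settle "which combination of baseline variables and time to negative STI test in clinic should be included as auxiliary variables in the imputation model". No other class of variable is named.
- **Data collection.** "The primary outcome will be assessed using chlamydia and gonorrhoea tests collected by post at 1 year and clinic records of completed tests". Separately, "At 4 weeks and at 1 year, postal questionnaires will be sent to all participants to collect self-reported data". Answers may come by web form, on paper or by telephone, and "Non-responders will be contacted by any method the participant agrees to at enrolment (post, email, text message, telephone call").
- **Secondary outcomes at 1 year.** The first item is "Diagnosed with any STI after joining the trial according to self-report", to be confirmed by postal results and clinic records. Number of partners, new partners and condom use follow.
- **Sample size calculation.** Losses to follow-up of 20% are allowed for.

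**The concern.** Imputation under missing at random is only as credible as the variables in the model. The article sets a sensible criterion and then names a pool that omits the data closest to the missing result. A sample has to be taken and posted, whereas the questionnaire can be answered online or by telephone, so a participant can have a questionnaire and no test result. That participant's report of a diagnosis, of partners and of condom use would not inform the imputed value.

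Two further features make the choice hard to explain. Time to a negative clinic test is itself measured after randomisation, so post-baseline data are not excluded on principle. And the Analysis section relies on predictors of loss to follow-up, while the selection step describes no search for them.

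At stake is the primary odds ratio. At 20% losses, 0.20 × 6250 = 1250 participants would have an imputed outcome.

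**Working it through.** The plan states no figure on this point, so there is none to reproduce. The calculation shows how large the effect could be.

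**Inputs from the article:** risks 20% (control) and 16% (intervention); 20% of results missing.

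**Assumed inputs:** self-reported diagnosis S is 60% sensitive and 98% specific for the 1-year result Y; S is available for half of those without a test; missingness depends on S only; imputation is within arm; total missingness is 20% in each arm.

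**Formulas, for an arm with risk p:**

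- P(S=1) = 0.6p + 0.02(1 − p)
- r1 = P(Y=1 | S=1) = 0.6p / P(S=1); r0 = P(Y=1 | S=0) = 0.4p / P(S=0)
- m0 and m1 are the missingness probabilities for S=0 and S=1, with odds(m1) = k × odds(m0), solved so that the total is 20%
- Without the questionnaire, the imputed risk equals the risk among the tested: [P(S=1)(1 − m1)r1 + P(S=0)(1 − m0)r0] / 0.8
- With it, untested participants who have S are imputed at r1 or r0. For the others, S is first imputed from everyone whose S is known.

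**Worked case: self-report doubles the odds of no test in control only.**

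- Control: P(S=1) = 0.12 + 0.016 = 0.136; r1 = 0.12/0.136 = 0.882; r0 = 0.08/0.864 = 0.0926; m0 = 0.183, m1 = 0.309.
- Without: (0.136 × 0.691 × 0.882 + 0.864 × 0.817 × 0.0926)/0.8 = 0.148/0.8 = 0.185, against a true 0.200.
- Intervention: missingness is unrelated to S, so the risk stays at 0.160. OR = (0.160/0.840)/(0.1853/0.8147) = 0.84.
- With: tested 0.1483 + untested with S 0.0259 + untested without S 0.0193 = 0.1935. OR = (0.160/0.840)/(0.1935/0.8065) = 0.79.

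**Results (true OR = (0.16/0.84)/(0.20/0.80) = 0.762):**

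| Odds of no test if self-report is positive | OR without questionnaire | OR with it, 50% available | OR with it, 10% available |
|---|---|---|---|
| doubled in both arms | 0.76 | 0.76 | 0.76 |
| doubled in control only | 0.84 | 0.79 | 0.83 |
| doubled in control, quadrupled in intervention | 0.67 | 0.72 | 0.68 |

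Total missingness is 20% in both arms in every row, so balanced totals would not reveal the problem.

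**Scale.** With 0.8 × 6250 / 2 = 2500 analysed per arm, the SE of the log OR is about √[1/(2500 × 0.20 × 0.80) + 1/(2500 × 0.16 × 0.84)] = √(0.00250 + 0.00298) = 0.074. Without the questionnaire the shifts are ln(0.837/0.762) = 0.094 and ln(0.673/0.762) = −0.124, or 1.3 and 1.7 SE. With it they are 0.041 and −0.051, or 0.6 and 0.7 SE.

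**Clinic records.** Suppose records already supply the positive result for a share c of truly infected self-reporters who would otherwise be missing, so that their missingness becomes (1 − c)m1. Without the questionnaire the two differential rows become 0.80 and 0.72 at c = 50%, and 0.78 and 0.74 at c = 80%.

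**Lower event rate.** At the blinded rate of 15.6% (17.3% v 13.9%, true OR 0.768), assume sensitivity 40–70%, specificity 97%, and missingness among self-reporters of 20% in one arm and 30% in the other. The OR is 0.70–0.73 or 0.81–0.84 without the questionnaire, and 0.74–0.75 or 0.79–0.80 with it at 50% availability.

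**4-week items.** A large-sample simulation assumed a 4-week behaviour with OR 2 to 3 for both infection and missingness and a 10-point difference between arms. Leaving it out moved the risk difference by 0.1 to 0.2 points, against an SE of √(0.20 × 0.80/2500 + 0.16 × 0.84/2500) = 1.1 points.

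**The case against.** The strongest objection is that the primary outcome already draws on clinic records, which are to be searched for positive diagnoses since joining. Many real diagnoses would then be observed positives and not missing results. This stands, and the clinic-records calculation shows how far it shrinks the shift. The capture rate is not stated, and records do not help with partners or condom use.

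Second, the 1-year kit and questionnaire share a postal request, so non-return of the two may overlap. The article gives no figure for those with a questionnaire but no test. This stands too: at 10% availability little is gained.

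Third, the details may be in the statistical analysis plan. It could widen the list, but the article does not leave the pool open: it names it. The point concerns what the article fixes.

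Fourth, delta-method and complete-case analyses are planned. The first probes departures from missing at random and the second drops the incomplete records. Neither uses the questionnaire information.

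A reader might go further in three ways that the document does not support:

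- That the planned estimate is biased. On the OR scale this needs missingness by self-report to differ between arms. Participants know their allocation, so a difference is possible, but nothing in the article shows one.
- That adding the questionnaire restores the true effect. The correction is partial unless nearly all untested participants have answered.
- That chained equations would invent a test time for people with no negative clinic test. The article does not describe the coding, and a separate category or indicator fits its wording.

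**Conclusion.** The point holds as an improvable choice in the primary analysis. The named pool is narrower than the article's own criterion for auxiliaries, and the selection step does not follow up the predictors of loss to follow-up on which the Analysis section relies. Widening it would make missing at random more plausible and add some precision. It is not a demonstrated bias.

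On the planned scale the gain in bias ranges from nothing, when missingness by self-report is equal across arms, to a little over half of the log-OR shift in the two differential cases at 50% availability. These sizes rest on assumed sensitivity, specificity, availability and arm-specific missingness, none of which the article gives. The 1-year items carry the case; the 4-week behaviours add little.

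**What to change.** In Supplementary analyses, and in the statistical analysis plan if it carries the same list:

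1. Add the 1-year questionnaire items to the candidate auxiliaries: self-reported STI diagnosis, number of partners, new partners and condom use. List the 4-week behaviours as lower-value candidates.
2. Let the independent statistician retain variables that predict either the outcome or its missingness. The selection can still be done without the treatment variable.
3. Report, by arm, how many participants without a test result answered the 1-year questionnaire, so that readers can judge how much the added variables contribute.

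The data are already being collected, so the cost is wording, settled before unblinding, and a somewhat larger imputation model. The downside is that the added auxiliaries are themselves incomplete and must be imputed in the same chain.

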#### Subgroup analyses

A limited number of subgroup analyses will be undertaken adjusting for other key predictors of outcome. Subgroup analyses include: age,^16–24^ sexual orientation (men who have sex with men or men and women, men who have sex only with women, women who have sex with men or men and women, women who only have sex with women), ethnic group (Caucasian, Black, other) and age at which left education (16 or under, 17 or over). The subgroups will be analysed by inclusion of an interaction term between treatment group and the subgroup in the appropriate regression model for the outcome. Data will be presented by categories of subgroup using effect estimates and 99% CIs. For each subgroup analysis, missing outcomes will be imputed consistent with the hypothesis of an interaction.^35^

#### Process outcomes

Candidate questionnaire items were identified for the measurement of the following constructs: attitudes towards partner notification, self-efficacy in telling a partner about an infection, self-efficacy in negotiating condom use, correct condom use self-efficacy, knowledge related to STIs. At 4 weeks, each of the five process outcomes were measured using the candidate questionnaire items (three to five items per process outcome). Based on these items, we will carry out confirmatory factor analysis to refine and identify a valid measurement model. For the main trial analyses, the final measurement model will be combined with the intervention group allocation, along with key baseline predictors, extending the measurement model to a Multiple Causes Multiple Indicators model. This model will be used to estimate the effects of the intervention on the five hypothesised process outcomes.

#### Economic evaluation

The economic modelling required to assess the cost-effectiveness of the intervention will estimate the annual probability of members of the target group acquiring chlamydia, gonorrhoea and NSU with and without the intervention (based on the experience of those in the control and intervention arms of the trial). Detailed information will be collected on the costs of delivering the intervention. Secondary sources will be used to estimate the future National Health Service (NHS) costs avoided as a consequence of avoided infections.

### Patient involvement

Patients were involved in the development of the intervention^15^ and the design of the trial materials and follow-up procedures.^36^ A patient is also a member of the Trial Steering Committee. Young people will be involved in the dissemination of the trial results.

### Monitoring

The safetxt trial will not have a separate Data Monitoring Committee. No interim analyses of intervention effects will be conducted since the trial is of a behavioural support intervention unlikely to cause harm, and therefore, there are no stopping rules. Analysis of intervention effects will be conducted once at the end of the trial. The sponsor may audit the trial per their own risk assessment and schedule.

Harms will be assessed by self-reported data. Car accidents are the only demonstrated harm resulting from text messaging, hence the intention to collect data regarding involvement in road traffic accidents. The safetxt intervention aims to increase partner notification of STI status. Fear of partner violence has been reported to be a barrier to partner notification and partner notification has been identified as a factor which may trigger partner violence. However, no randomised controlled trials targeting increased partner notification detected a difference in partner violence between the control intervention groups. Data will be collected regarding the experience of partner violence at 12 months.

In addition, participants will be asked an open-ended question in the 12-month questionnaire: ‘Did anything good or bad happen as a result of being involved in the study or receiving the text messages? Please describe.’ The Clinical Trials Unit will keep detailed records of all adverse events reported. Reports will be reviewed by the Principal Investigator and the TSC to consider intensity, causality and expectedness. As appropriate, these will be reported to the sponsor and the Ethics Committee.

### Ethics and dissemination

All trial participants will provide written informed consent prior to enrolment in the trial. Participants’ can withdraw from the trial on request. Participant will receive usual NHS care there is no ancillary care.

Any modifications to the protocol will be approved by the ethics committee prior to implementation. Records of any important modifications will be submitted as an addendum in the journal in which this protocol is published.

Trial results will be published open-access in peer-review journals. Authorship will be on the basis of meeting the criteria recommended by the International Committee of Medical Journal Editors.

After the publication of our main trial findings, the anonymised trial data set will be available on request from the corresponding author.

## Discussion

STIs such as chlamydia and gonorrhoea confer a heavy burden of disease among young people with long-term sequelae such as infertility. Safer sex behaviours such as condom use, notifying partner(s) about an existing STI and STI testing reduce the risk of STI, but young people may lack the knowledge, confidence and skills needed to adopt these behaviours. Safer sex interventions delivered by mobile phone are acceptable to young people and show promise in increasing safer sex behaviours, but to date their effects on STI are not reliably known.

If it proves to be effective, this low-cost intervention could have an important impact in improving sexual health and reducing inequalities among young people in the UK. There is likely to be international interest in the impact of the intervention as short written messages delivered via mobile phones are increasingly used for behavioural support worldwide and sexually transmitted infections remain an important cause of morbidity and mortality.
